### Protocol drop-out

Nebulization of study medication can be discontinued temporarily when heparin-induced thrombocytopenia (HIT) is suspected. Nebulization of study medication is definitely discontinued when HIT is confirmed. Furthermore, nebulization of study medication can be discontinued temporarily in case of surgical procedures, clinically relevant bleeding (mandating infusion of clotting factors, fresh frozen plasma or platelet concentrates), activated partial thromboplastin time of > 150 seconds and a platelet count of ≤ 10 × 10^9^/L. Finally, study medication can be discontinued temporarily with appearance of excessive blood in sputum or lavage fluids. Timing of re-start is left to the discretion of the attending physician, but it is stressed to re-start study medication as soon as it is considered safe. In case of any life-threatening bleeding event, protamine sulphate can be used as an *antidotum* to heparin, at the discretion of the attending physician.

### Concomitant medication

Intravenous or oral anticoagulant therapy, if indicated, is allowed. Routine use of N-acetylcysteine or any other mucolytic agent, either nebulized or directly installed into the airways, is not allowed. They should only be used when viscous mucus is considered problematic, at the discretion of the attending physician.

### Standard procedures

Attending physicians are advised to use lung-protective ventilation strategies, including the use of lower tidal volumes (≤ 6 mL/kg predicted body weight) or lower airway pressures (≤ 30 cmH_2_O). Levels of positive end-expiratory pressure (PEEP) and inspired oxygen (FiO_2_) are titrated on PaO_2_, preferably using a PEEP/FiO_2_ table, and according to local guidelines. If spontaneous ventilation is well tolerated, it is used from then till the end of ventilation. Thereafter, weaning from ventilation is performed by stepwise lowering of pressure-support level, or by spontaneous breathing trials, according to local guidelines. As soon as patients are ready to be weaned from the ventilator, the pressure-support level is lowered stepwise to 5 cmH_2_O. In case of spontaneous breathing trials, the patient’s ability to breathe spontaneously is verified for 30 minutes using a T-piece or continuous positive airway pressure. Patients are assessed daily if they are ready to be tracheally extubated. Extubation criteria are as follows: patient is responsive and cooperative, has an adequate oxygenation (saturation > 90%) with PaO_2_/FiO_2_ of 150 mmHg or more and FiO_2_ of 40% or less, is hemodynamically stable with no uncontrolled arrhythmia, and has a rectal temperature > 36.0°C. Attending physicians are advised not to perform tracheotomies in the first 14 days after inclusion. If a patient meets extubation criteria, but remains intubated because of planned surgeries requiring general anesthesia, this is reported.

Analgo-sedation and fluid management are according to local guidelines. Analgo-sedation is achieved by continuous or bolus infusion of either fentanyl or morphine in combination with a benzodiazepine or propofol, titrated to individual needs. Procedure-related analgesia and sedation are at the discretion of the attending physician. Sedation depth is measured on a daily basis, and is used to titrate infusions of sedatives.

In general, patients are resuscitated using buffered hypertonic or isotonic saline solutions, targeting a urine output of 0.5 to 1.0 ml/kg/h. If necessary to maintain serum albumin concentration > 15 g/L, human albumin is administered. After the first 24 hours, fluid administration is dictated by clinical needs.

Antibiotic prophylaxis and thromboprophylaxis are applied in accordance to local guidelines. We chose to allow the use of systemic or oral anticoagulants. Although we expect that the use of (intravenous) anticoagulant agents and prophylactic antibiotics will be similar in both groups, we will record the use of these agents.

### Follow-up

On the day of ICU admission, demographic and baseline data, as well as data on disease severity and extent of burn injury are collected. Data collection includes: gender, age, height, weight, functional status (independent, partially dependent or totally dependent), cardiac status (heart failure, according to the New York Heart Association (NYHA) [17], acute coronary syndrome *or* persistent ventricular tachyarrhythmia), alcohol status (in the past two weeks: 0 to 2 drinks/day, or more than 2 drinks/day), smoking status (in the past three months: never, former, or current). Data collection on relevant medical history include: COPD for which inhalation therapy or oral steroids are used, respiratory infection in the last month (upper or lower), history of active cancer, weight of loss more than 10% in the last six months, history of diabetes mellitus, chronic kidney disease, liver failure (Child-Pugh classification) [18], acquired immunodeficiency syndrome and use of relevant medications (including oral anti-diabetics, antibiotics in the last three months, statins, and corticosteroids). Regarding extent of burn injury, collected data include TBSA, partial or full thickness burn, Belgian Outcome in Burn Injury Study Group Index [19] and the Abbreviated Burn Severity Index (16).

Data on standard of care and clinical outcome variables (described below) are collected on a daily basis for the maximum duration of 28 days, until first discharge from ICU or death (whichever comes first). Data on length of stay in ICU and - hospital, mortality in ICU and hospital, and re-admissions to ICU are assessed on days 28 and 90 (Table 2).

**Table 2 T2:** Time schedule of study procedures

	**Day of admission (day 1)**	**Every day**^ **b/c** ^	**Days 1, 3, 5, 7, 9, 11 and 13**^ **c** ^	**Day of hospital discharge**	**Day 28**	**Day 90**
Screening and randomization						
screening^a^	X					
demographic data	X					
inclusion criteria	X					
exclusion criteria	X					
informed consent	X					
randomization	X					
Before start study medication						
blood sampling	X					
non directed broncho-alveolar lavage sampling	X					
Clinical procedures						
chest X-ray		X				
nebulization of study medication^c,d^		X				
blood sampling^c^			X			
non-directed broncho-alveolar lavage sampling^c^			X			
Clinical data collection						
%TBSA	X					
SAPS II	X					
Karnofsky score	X					
ABSI	X					
SOFA score		X				
LIS/OI		X				
ventilatory settings		X				
relevant medications^e^		X				
sedation		X				
fluid balance		X				
Other data collection						
adverse event		X				
use of blood products		X				
use of protamine		X				
use of n-acetylcysteine		X				
use of vasopressors^f^		X				
bronchoscopy^g^		X				
pneumonia (VAP)		X				
date of hospital discharge				X		
Survival, if not:				X	X	X
date of death						
cause of death						

^a^Of all patients with suspected inhalation injury.

^b^For the maximum duration of 28 days.

^c^For the maximum duration of 14 days or until the patient is successfully weaned from mechanical ventilation.

^d^If temporarily or definitely discontinued, reason should be registered.

^e^Such as antibiotics, immunosuppressives, systemic anticoagulants.

^f^Such as dopamine, dobutamine, norepinephrine, or epinephrine.

^g^To remove foreign particles and accumulated secretions.

The following variables are collected daily: ventilator freedom (described below), requirement for non-invasive mechanical ventilation (if yes: indication and duration per day), Oxygenation Index (OI) [20], Sequential Organ Failure Assessment (SOFA) scores [21], Lung Injury Score (LIS, based on chest X-ray findings, PaO_2_/FiO_2,_ PEEP level and respiratory compliance) [22], presence of ventilator-associated pneumonia (VAP), presence of acute respiratory distress syndrome (ARDS) [23], number of bronchoscopy-guided cleaning attempts per day to clean the larger airways, and use of relevant medications (including antimicrobial agents, immunosuppressive agents, and any anticoagulant agent).

The following laboratory data are collected daily: glycemia, urea, creatinine, aspartate aminotransferase, alanine aminotransferase, bilirubin, hemoglobin (Hb), platelets, prothrombin time (PT), aPTT, white blood cells count, albumin, and arterial blood gas analysis.

Typical ICU-related therapy variables to collect daily include: ventilation variables, need for lung rescue therapy (such as prone ventilation, extracorporeal membrane oxygenation or oscillator), analgo-sedation variables (including sedations scores, using for example, the Richmond Agitation Sedation Scale (RASS) [24], and delirium scores, using for example, the Confusion Assessment Method (CAM-ICU) [25], pain score using, for example, a 10-point score, cumulative dose of sedatives and analgesics (including fentanyl, morphine, midazolam, and propofol), and fluid resuscitation variables including cumulative fluid balance [26], amount and type of infused fluids (for example, crystalloids, colloids and albumin), and daily amount of enteral/parenteral nutrition [27]. After the first 14 days, data on tracheotomies are collected.

Any surgical procedure, the amount of blood loss, presence of serious bleedings (defined as any clinically important bleeding from the lung (prompting bronchoscopy) or any clinically important bleeding requiring surgery or transfusion of clotting factors or blood products (red cells, platelets, plasma) is reported. Type and number of units transfused are specified as well as reasons to (temporarily) discontinue study medication, as described above, are reported as well.

### Study endpoints

The primary endpoint - is the number of ventilator-free days, defined as the number of days alive and breathing without the assistance of a ventilator during the first 28 days. Thus, a patient must be free of ventilation for 24 hours to have one ventilator-free day. If, after successful extubation the patient requires re-intubation and ventilation due to a surgical procedure, this episode will not count as a ventilator day. However, if after surgery, ventilation is prolonged due to respiratory insufficiency, the day(s) will be counted as ventilator days.

Secondary endpoints - are subdivided into clinical and laboratory outcome variables and safety variables. Clinical outcome variables include: (a) length of stay (ICU and hospital); (b) mortality (28- and 90-day); (c) mortality (ICU and hospital); (d) daily LIS; (e) daily OI; (f) daily SOFA scores; (g) cumulative dosages of sedatives; (h) incidence of VAP; (i) total number of bronchoscopy-guided cleanings of the larger airway. Laboratory outcome variables include: (a) levels of markers of coagulation and fibrinolysis in blood and lung lavage fluid, including but not limited to tissue factor, activated factor VII, antithrombin, thrombin-antithrombin complexes, activated protein C, plasminogen activator activity, tissue plasminogen activator, urokinase plasminogen activator, plasminogen activator inhibitor 1, fibrin degradation products and plasma levels of heparin; (b) levels of markers of inflammation in blood and lung lavage fluid, including but not limited to IL-1beta, IL-6, IL-8, IL-10, TNF-alpha, growth factors and markers of complement activation; and (c) biological markers of lung injury in blood and lung lavage fluid, including but not restricted to total protein, albumin and IgM, Clara Cell 16 protein and soluble receptor for advanced glycation endproducts. Safety variables include (a) occurrence of relevant bleedings - requiring surgery, requiring transfusion of clotting factors, requiring transfusion of blood products (red cells or platelets or plasma), any clinically important bleeding from the lung (prompting bronchoscopy); (b) any other transfusion of blood products - red cells or platelets or plasma; (c) confirmed HIT; and (d) prolonged activated partial thromboplastin time (aPTT > 150 seconds).

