Interim analysis - blind interim analysis for safety is performed after 58 patients are successfully included and reached the endpoint. Suspected unexpected serious adverse events (SUSARs) and serious adverse events (SAEs) (any death; all serious bleedings requiring surgery, transfusion of clotting factors or blood products; any clinically important bleeding from the lung; requirement of transfusion of blood products; and confirmed heparin-induced thrombocytopenia) that are possibly related to study medication will be compared using the Chi-square test. If the data safety monitoring board (DSMB) (see below) has concern regarding the incidence of serious adverse events, it can request unblinded data. The investigators will remain blinded for the groups until the study is completed. If complications occur significantly more often in the intervention group (*P* ≤ 0.05), the study is terminated due to harm.

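### Minor, cheap improvement: outside the lung a bleed counts only if it required surgery, clotting factors or blood products, so a rare life-threatening bleed managed otherwise is missing from the bleeding variable

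*Protocol article*

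**What the plan says.** All references are to the protocol article. Three places fix how bleeding is counted.

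- **Follow-up** defines serious bleeding as clinically important lung bleeding that prompts bronchoscopy, or "any clinically important bleeding requiring surgery or transfusion of clotting factors or blood products".
- **Study endpoints**, safety variable (a), counts "occurrence of relevant bleedings - requiring surgery, requiring transfusion of clotting factors, requiring transfusion of blood products", and again clinically important lung bleeding. Variable (b) is "any other transfusion of blood products - red cells or platelets or plasma".
- **Statistical considerations**, interim analysis, lists "all serious bleedings requiring surgery, transfusion of clotting factors or blood products", alongside any death, clinically important lung bleeding, transfusion requirement and confirmed HIT. SUSARs and listed SAEs judged possibly related to study medication are compared by Chi-square. The study is to be terminated if complications are significantly more frequent on heparin (P ≤ 0.05).

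Other sections bear on the same patients.

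- **Protocol drop-out** provides for the antidote: "In case of any life-threatening bleeding event, protamine sulphate can be used".
- **Standard procedures**: "We chose to allow the use of systemic or oral anticoagulants".
- **Table 2** has daily rows for adverse events and "use of protamine", and a row for "cause of death".
- **Study organization** sends all SAEs and SUSARs to the DSMB within 24 hours of receipt at the coordinating center and lets the DSMB obtain unblinded data.

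**The concern.** The Discussion names serious bleeding as a major safety concern and raises the systemic effect of nebulized heparin as well as bleeding in the lung. Yet outside the lung every counting criterion is a treatment the bleed required. How dangerous the bleed was, and where it occurred, play no part. Lung bleeding is handled differently, since it qualifies without surgery or transfusion.

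Some grave bleeds do not call for surgery or blood products. A conservatively managed intracranial bleed is an example; it is the reviewer's, not the protocol's. The protocol recognises life-threatening bleeding as a category when it allows protamine, but protamine is neither surgery, a clotting factor nor a blood product, and its use is not a counting criterion. At stake is whether the variable that answers the main safety question includes the gravest events of the kind it is meant to measure.

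**Working it through.** The plan states no bleeding rate and no power for bleeding, so there is no figure of its own to reproduce. The check compares the definitions, followed by simple arithmetic on what one omitted patient amounts to.

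**Step 1. Apply the rules to each kind of bleed.** Interim entries apply to events judged possibly related to study medication.

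| Bleed | Safety variable (a) | Listed interim events |
|---|---|---|
| Clinically important lung bleed prompting bronchoscopy | Counted | Counted |
| Non-lung, required surgery, clotting factors or blood products | Counted | Counted |
| Non-lung, life-threatening, non-fatal, none of these required | Not counted | Not counted, unless a SUSAR |
| As the row above, but fatal | Not counted | Counted as a death |
| As the third row, but transfused for another reason | Not counted; transfusion falls in (b) | Transfusion counted, not the bleed |

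The safety list in Study endpoints opens with the word *include*, which might seem to leave room. The Follow-up section, however, gives its criteria as a definition, and the other two places repeat them.

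**Step 2. Weight of one patient.** With 58 per arm (Statistical considerations), 1/58 = 1.7 percentage points. At the interim after 58 patients, assuming equal arms of 29, 1/29 = 3.4 points.

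**Step 3. How often.** The document gives no rate, so any rate r is an assumption. The chance of at least one such bleed in an arm of 58 is 1 − (1 − r)^58.

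| Assumed r | Expected in 58 (58 × r) | Chance of at least one |
|---|---|---|
| 0.1% | 0.06 | 5.6% |
| 0.5% | 0.29 | 25% |
| 2% | 1.16 | 69% |

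The range is too wide to support a statement about frequency.

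**Step 4. Can one omission change the interim result?** For a heparin and b control patients with an event, 29 per arm, the uncorrected statistic is χ² = 58 × [a(29 − b) − b(29 − a)]² / [29 × 29 × (a + b) × (58 − a − b)].

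- 4 v 0: 58 × 116² / (29 × 29 × 4 × 54) = 4.30, P = 0.038.
- 3 v 0: 58 × 87² / (29 × 29 × 3 × 55) = 3.16, P = 0.075.
- 4 v 1: χ² = 1.97, P = 0.16.

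The plan does not say whether the listed events are tested singly or pooled, so assumed pooled counts are shown too: 18 v 10 gives P = 0.036, 17 v 10 gives P = 0.065 and 18 v 11 gives P = 0.066.

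A bleed omitted on heparin can thus hide a crossing (4 v 0 read as 3 v 0; 18 v 10 read as 17 v 10). One omitted on control can create a crossing (4 v 1 read as 4 v 0; 18 v 11 read as 18 v 10). All these counts were chosen to sit at the boundary. With a continuity correction none of the tables reaches 0.05. By Fisher's exact test, 4 v 0 gives P = 0.11 and 3 v 0 gives P = 0.24, so that change of result disappears.

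**The case against.** The strongest reply is that this is a defensible design choice. The three definitions agree with one another. Protocol drop-out likewise describes clinically relevant bleeding by the treatment it calls for. Such criteria need less judgement than a severity grade. The omitted patient is also hard to find: the bleed must be life-threatening, outside the lung and managed without surgery, clotting factors, red cells, platelets or plasma. To be missing from the interim list as well, the patient must survive and have no other listed event. Patients with a clinically important bleeding disorder are excluded at entry.

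Most of this stands, and it is why the point is minor. There is no contradiction, and few patients are likely to be affected. It does not remove the point, because the document itself fixes the counting rule, and that rule leaves out a grave form of the event it is meant to measure.

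A reader might infer more, and the documents do not support it.

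- *That such bleeds go unreported.* They do not. Adverse events are recorded daily, cause of death is recorded, and all SAEs go to the DSMB, which can ask for unblinded data. What is missing is the entry in variable (a) and in the listed interim events.
- *That the stopping rule is compromised.* This needs a result exactly at the boundary and the uncorrected Chi-square. In a pooled comparison the omitted patient must also have no other listed event.
- *That the omission favours heparin.* Systemic anticoagulants are allowed in both arms, so an omitted bleed can fall in either.
- *That the protocol plans to treat life-threatening bleeding with protamine alone.* It permits protamine at the physician's discretion and says nothing about it replacing surgery or transfusion.

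**Conclusion.** The concern holds as a minor, inexpensive improvement. Outside the lung, a rare non-fatal life-threatening or critical-site bleed managed without surgery, clotting factors or blood products is absent from safety variable (a) and, unless it is a SUSAR, from the listed interim events. A fatal one may appear only as a death.

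The conclusion about counting rests on the text alone. Its size and direction cannot be derived. The only firm quantity is the weight of each omitted patient in a final arm, 1.7 percentage points; the 3.4 points at the interim assume equal arms. The bleeding rates and event counts in the working are assumptions for illustration. No effect on the interim decision should be claimed beyond a possible boundary case under the uncorrected Chi-square.

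**What to change.** Before the interim analysis, add one limb to the serious-bleeding definition in Follow-up, to safety variable (a) in Study endpoints and to the interim list in Statistical considerations: *or any fatal, life-threatening or critical-site (for example intracranial) bleeding, or bleeding for which protamine was given, whatever the treatment*.

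Classify these bleeds from the SAE reports of the blinded investigators, together with the protamine and cause-of-death fields. A separate adjudication panel is not needed. Report the added subset by arm, so that the treatment-based count can still be read on its own.

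The sample size does not change. The cost is some clinical judgement about what is life-threatening, and a short amendment now that recruitment has started. Table 2 names the adverse-event and protamine rows but does not show that bleeding severity or the reason for giving protamine is recorded. The SAE reports of patients already enrolled may therefore need a check.

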### Collection of blood samples and lung lavage fluid

In selected centers, blood is drawn through the existing arterial line and processed immediately. A total volume of 20 mL is drawn every other day for a maximum period of 14 days, and always before performing the lung lavage. A non-directed lung lavage is performed every other day for a maximum period of 14 days or less if the patients are successfully weaned from mechanical ventilation. Lung lavage is performed as described before [28]. In brief, 20 ml sterile 0.9% saline is instilled via a standard 50 cm 14 gauge tracheal suction catheter. The distal end of the catheter is introduced via the endotracheal tube and advanced until resistance is encountered. Immediately after instillation of the saline solution over 4 to 5 seconds, fluid is aspirated before withdrawal of the catheter. Plasma and lung lavage fluid are centrifuged and stored at −80°C until assays (described above) are performed.

### Statistical considerations

Sample size calculation - in a previous trial testing the efficacy of nebulized heparin, critically ill patients requiring ventilation for at least 48 hours showed a reduction of 4.6 days of ventilation (mean (SD) 22.6 (4.0) versus mean (SD) 18.0 (7.1)) [29]. We conservatively estimate that the improvement in burn patients with inhalation trauma is less than in a heterogeneous group of critically ill non-burn patients. We consider a reduction of three days of ventilation clinically relevant. We require 58 patients per treatment arm to observe a difference in the number of ventilator-free days at day 28 with (α < 0.05 at 80% power). Although burn patients with inhalation trauma usually have fewer ventilator-free days than critically ill non-burn patients, the standard deviation appears to be similar between burn injury patients [30] and critically ill patients in general [31], indicating that the sample size of 58 per arm for a total of 116 is sufficient to observe an improvement of three ventilator-free days (nQuery Advisor Software version 7.0, Statistical Solutions Ltd, Cork, Ireland).

Stratification - considering the fact that TBSA is associated with prolonged duration of ventilation [32], we want to avoid an uneven distribution of the severity of burns between study groups. Therefore, patients are stratified based on TBSA (≥ 20% versus < 20%). Provided that this stratification will only be used to ensure an equal distribution, and stratification is based on the median TBSA, it does not affect the sample size of this study.

Interim analysis - blind interim analysis for safety is performed after 58 patients are successfully included and reached the endpoint. Suspected unexpected serious adverse events (SUSARs) and serious adverse events (SAEs) (any death; all serious bleedings requiring surgery, transfusion of clotting factors or blood products; any clinically important bleeding from the lung; requirement of transfusion of blood products; and confirmed heparin-induced thrombocytopenia) that are possibly related to study medication will be compared using the Chi-square test. If the data safety monitoring board (DSMB) (see below) has concern regarding the incidence of serious adverse events, it can request unblinded data. The investigators will remain blinded for the groups until the study is completed. If complications occur significantly more often in the intervention group (*P* ≤ 0.05), the study is terminated due to harm.

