**Discussion:**

As far as the authors know, HEPBURN is the first randomized, placebo-controlled trial, powered to investigate whether local treatment with heparin shortens duration of ventilation of intubated and ventilated burn patients with inhalation trauma.

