## Background

Inhalation trauma adds to the morbidity and mortality of burn patients [1,2]. Indeed, up to one third of burn patients require hospitalization due to inhalation trauma and a substantial percentage of these patients develop respiratory insufficiency. Moreover, approximately one third of burn patients with inhalation trauma eventually die, markedly more than burn patients without pulmonary involvement.

The underlying pathophysiology of inhalation trauma is only partly understood. Injury is thought to be at least the result of heat exposure to the airway mucosa or inhalation of noxious particles or toxic gases [3]. Injury of airway mucosa could induce an inflammatory response resulting in vascular leakage and pulmonary edema [4]. Pulmonary cast-formation could certainly play a role, since one study of burn patients shows disturbed alveolar fibrin turnover [5], and several preclinical studies show obstructive airway casts after smoke inhalation [6-9].

At present, therapy for inhalation trauma is merely supportive [10]. Animal models of smoke injury [6,7,9] and clinical trials of burn patients with inhalation trauma suggest that local treatment with heparin has beneficial effects [11,12]. The objective of the present trial is to determine the clinical efficacy and safety of frequent nebulizations of heparin in burn patients with inhalation trauma. Furthermore, the present trial investigates local effects of heparin on pulmonary coagulation and inflammation.

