Studies in healthy volunteers demonstrate that approximately 8% of nebulized heparin reaches the lower respiratory tract, of which 40% remains present 24 hours after inhalation [59]. The dose of nebulized heparin (applied as a single dose) that results in measurable increases in plasma aPTT is 150,000 IU and the half-life of the inhaled heparin is estimated to be 28 hours [60]. Since the type of nebulizer could affect the percentage of dose reaching the lower respiratory tract, we use the same nebulizer type as in previous clinical trials of nebulized heparin in critically ill patients [29,61]. In this trial, both dosing and duration of local heparin therapy are different from the two retrospective clinical studies of nebulized heparin in burn patients [11,12]. We based the dose, frequency and duration of heparin nebulization on a previous trial of critically ill patients, in which heparin nebulization was safe and associated with an increase in the number of ventilator-free days [29].

A major concern regarding safety could be the occurrence of serious bleedings. It might be argued that, due to endothelial injury and the increased vascular permeability resulting from the inhalational injury, the systemic impact of nebulized heparin and the risk of pulmonary bleedings might be higher in burn patients with inhalation injury when compared to critically ill patients without inhalation injury. However, two preclinical studies of burn and smoke inhalation injury models reported that heparin nebulization did not affect the systemic clotting time [6,9]. To date, data on safety of local heparin treatment in burn patients with inhalation trauma are limited. HEPBURN stops if complications occur significantly more often in one arm.

We chose the number of ventilator-free days at day 28 as the primary endpoint of this trial, a clinically relevant outcome parameter in critically ill patients. The effect of heparin may vary depending on the severity of injury [6]. However, the sample size of this trial does not allow subgroup analyses, for example, the evaluation as to what extent the efficacy of heparin depends on the severity of burn injuries.

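### The sample size section treats three fewer days of ventilation as three more ventilator-free days; the trial is powered for the second, not, as the abstract says, for shorter ventilation.

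*Protocol article*

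**What the plan says.** All references are to the protocol article.

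- **Statistical considerations, sample size calculation.** The earlier nebulized-heparin trial is said to have "showed a reduction of 4.6 days of ventilation (mean (SD) 22.6 (4.0) versus mean (SD) 18.0 (7.1". The target follows: "We consider a reduction of three days of ventilation clinically relevant". The paragraph ends by saying that 58 per arm "is sufficient to observe an improvement of three ventilator-free days". It gives no conversion between the two units and no mortality assumption.
- **Study endpoints.** The primary endpoint is "the number of days alive and breathing without the assistance of a ventilator during the first 28 days". 28-day and 90-day mortality are secondary endpoints. Duration of ventilation is not on the secondary list.
- **Abstract, Discussion.** The trial is described as "powered to investigate whether local treatment with heparin shortens duration of ventilation of intubated and ventilated burn patients with inhalation trauma".
- **Discussion, on dose selection.** Of the same earlier trial it says that "heparin nebulization was safe and associated with an increase in the number of ventilator-free days".
- **Discussion, concluding paragraph.** Here the trial is said to be powered for an increase in VFDs.
- **Background.** "approximately one third of burn patients with inhalation trauma eventually die".
- **Statistical analysis.** A Kaplan-Meier and log-rank analysis of freedom from ventilation is planned, with hazard ratios and 95% confidence limits.

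**The concern.** Two quantities share one number. For a patient alive at day 28, ventilated days and VFDs add up to 28, apart from the rule that re-ventilation for surgery is not counted. A patient who dies on the ventilator on day 5 has 5 ventilated days and no VFDs, so the identity fails. Each death separates the two measures.

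This has three consequences.

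- The effect called clinically relevant, read as worded, is larger than the VFD effect it would produce, so the power quoted for VFDs does not carry over to it.
- A gain in VFDs can come partly from survival, so it is not in itself evidence of shorter ventilation.
- The article describes what it is powered for in two ways, once in the abstract and once in its conclusion, and only the second matches the calculation.

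The earlier trial's contrast is also labelled in two ways: as fewer days of ventilation in the sample size paragraph and as more VFDs in the Discussion.

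**Working it through.** **Inputs from the article:** difference 3; SDs 4.0 and 7.1; 58 per arm; α 0.05 (two-sided assumed); power 80%.

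**Step 1, reproduce the stated figure.** Root-mean-square SD = √[(4.0² + 7.1²)/2] = √33.2 = 5.76.

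n per arm = 2 × SD² × (1.96 + 0.84)² / 3² = 57.9, rounded up to 58. Power at 58 per arm is 80.1%.

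Other choices miss the figure: SD 7.1 gives 88, SD 4.0 gives 28, the plain average 5.55 gives 54, and a one-sided test gives 46. So 58 is the number for 3 VFDs at SD 5.76, with no reserve.

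**Step 2, convert three fewer ventilated days into VFDs.** Assume that a fraction m dies in each arm and scores zero, and that everyone else is ventilated three days less under heparin. The mean VFD difference is 3 × (1 − m). With the SD held at 5.76:

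| m (assumed) | VFD difference | Power at 58 per arm | n per arm for 80% |
|---|---|---|---|
| 0% | 3.0 | 80% | 58 |
| 10% | 2.7 | 71% | 72 |
| 20% | 2.4 | 61% | 91 |
| 33% | 2.0 | 46% | 131 |

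To reach 3 VFDs through ventilation time alone, the others would need 3/(1 − m) fewer days: 3.3, 3.8 and 4.5 for the three non-zero rows.

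**Step 3, a pessimistic bound.** Zeros also widen the spread. Use SD = √[(1 − m) × 5.76² + m(1 − m) × μ²], where μ is the mean VFDs of non-zero patients across the two arms, and assume a control-arm mean of 12 to 18 in those patients (so μ = 13.5 to 19.5). Power is then 57–44%, 41–28% and 28–18% for m = 10%, 20% and 33%. If the SDs 4.0 and 7.1 describe VFDs, they may already include deaths, in which case this counts them twice. The table in step 2 is therefore the one to rely on.

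**Step 4, the reverse direction.** Suppose ventilation in survivors does not change and they average 18 VFDs (assumed). A gain of 3 VFDs then needs mortality to fall by 3/18 = 16.7 points, from 33% to about 17%. From 10% mortality it cannot happen: even at an average of 20 VFDs, removing every death adds only 0.10 × 20 = 2.0.

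**The case against.** The strongest reply is that this is a slip in labelling. The endpoint, the last sentence of the sample size paragraph and the article's conclusion all speak of VFDs, and 58 per arm is right for them. The power losses arise only if the three-day target is taken literally as ventilation time. The Background states the objective as clinical efficacy and safety and does not name ventilation time. All of this stands, and it limits the point to the wording of the target and of the claim.

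Four stronger readings are tempting, and the article does not support them.

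- **The sample size is wrong, or the trial cannot inform on ventilation.** The number is correct for the actual endpoint. What fails is the statement of power for a different quantity.
- **Ventilation time is analysed nowhere.** It is missing from the secondary list, but the Kaplan-Meier analysis of freedom from ventilation is planned and 28-day mortality is a listed endpoint. Together they partly show where a VFD gain comes from. No power is claimed for either.
- **One third of the enrolled patients will die by day 28.** The Background figure is eventual mortality in burn patients with inhalation trauma generally. Patients unlikely to survive beyond 72 hours and those with burns over 60% of body surface are excluded, so 33% is an upper value.
- **A positive result could easily be due wholly to fewer deaths.** Step 4 shows that this needs a very large fall from high mortality, which the 28-day mortality endpoint would be expected to display.

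Nor does a patient still ventilated at day 28 break the equivalence when duration is counted to day 28: 28 ventilated days and no VFDs still add up to 28.

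**Conclusion.** The point holds as a mismatch between the stated target and claim and what was calculated. The trial has 80% power for 3 VFDs. For three fewer days of ventilation in patients who do not score zero, power is about 71%, 61% or 46% at m = 10%, 20% or 33%. The abstract's statement of power for shorter ventilation is therefore unsupported as written, and a VFD difference alone would not establish it.

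The figures rest on equal mortality in the arms, zero VFDs for every death (the article does not say how a death after extubation is scored), and an unchanged SD of 5.76. No 28-day mortality is given for the enrolled population, so the range of m is assumed.

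Reading 22.6 versus 18.0 as VFDs rests on the Discussion's description of the same trial and on the use of those SDs to size a VFD endpoint; the Discussion does not repeat the two means. Sample size, primary endpoint and primary test need no change on this account.

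**What to change.** 1. In the sample size calculation, state the clinically relevant effect as three VFDs throughout and remove the equation with three days of ventilation.
2. Relabel 22.6 versus 18.0 as VFDs, after checking the source, so that the paragraph agrees with the Discussion.
3. Reword the abstract's claim of power to match the concluding paragraph.
4. Report beside the primary result: 28-day mortality, the planned freedom-from-ventilation analysis, and ventilation duration to day 28 in day-28 survivors. The last is supportive only, because it conditions on survival, and should not be a condition for any claim.
5. Describe a positive primary result as more ventilator-free days and not, by itself, as shorter ventilation.

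The cost is wording plus one extra summary from data already collected daily to day 28. The price is a more modest headline claim.
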